### Primary outcome measures

The primary outcomes of the HAPPY trial are changes in patient adherence and persistence at the end of six months. These will be measured subjectively using the self-reported Morisky scale [16] and the Tool for Adherence Behaviour Screening (TABS) [17] and objectively using the medication refill data (e.g. MedsIndex score [18]). The Morisky scale assesses both intentional and unintentional nonadherence and comprises four items. Responses for each item are scored 0 for 'yes' and 1 for 'no' (except for the item 'are you always careful in taking medicines?' where the score was reversed) and added together. A total score of zero represents good adherence and a score of one or more represents suboptimal adherence. The TABS is another self-reported adherence measure, which was originally developed in Australian patients using chronic medicines. It has two subscales - 'adherence' and 'nonadherence' - each comprising four items to be answered on a 5-point Likert-type scale ('never' - 1 to 'always' - 5). The total score for 'nonadherence' will be subtracted from that of 'adherence'; a differential of ≥15 will be regarded as good adherence and ≤14 will be regarded as suboptimal adherence. The TABS measures both intentional and unintentional deviations from recommended management and has been shown to have greater incremental validity than other self-reported adherence measures [17]. The MedsIndex gives each patient a score out of 100 for each of their long-term medications, which is calculated based on their refill history. Any score less than 100 suggests suboptimal adherence.

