### Data analysis

Participant characteristics in the UCG and PCG will be compared at baseline. Paired t-tests and/or Wilcoxon Signed Rank test will be used to compare changes in total scores on the Morisky scale, TABS and MedsIndex between the PCG and the UCG at baseline and six months. MedsIndex scores will be compared using paired t-tests and/or Wilcoxon Signed Rank test in the UCG and the HCG at six months.

Baseline data will be used to identify factors associated with suboptimal adherence in the whole study population. Significant factors in univariate analysis (chi-square, Mann-Whitney U test and Student's t-test) will be further tested in multivariate analysis (linear regression) to identify independent predictors of nonadherence/nonpersistence in the study population. To adjust for cluster randomisation, a pharmacy variable will also be included in the multivariate models.

An economic evaluation will also be carried out and will be reported elsewhere.

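### The baseline predictor analysis pairs an outcome defined by cut-offs, and screening tests that fit it, with linear regression; the outcome should be named and the model and screening matched to it

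*Protocol article*

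**What the plan says.** The second paragraph of Data analysis in the Protocol article opens with its aim: "Baseline data will be used to identify factors associated with suboptimal adherence in the whole study population". Candidates are filtered first: "Significant factors in univariate analysis (chi-square, Mann-Whitney U test and Student's t-test" is the wording up to the closing bracket. Those that survive "will be further tested in multivariate analysis (linear regression) to identify independent predictors of nonadherence/nonpersistence in the study population". Pharmacy is handled in one sentence: "To adjust for cluster randomisation, a pharmacy variable will also be included in the multivariate models". The text does not say which variable is regressed, or in what form pharmacy enters.

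Primary outcome measures gives the meaning of suboptimal adherence, each time as a cut-off:

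- Morisky: "A total score of zero represents good adherence and a score of one or more represents suboptimal adherence".
- TABS: "a differential of ≥15 will be regarded as good adherence and ≤14 will be regarded as suboptimal adherence".
- MedsIndex: "Any score less than 100 suggests suboptimal adherence".

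The same instruments also yield numeric scores, and the first paragraph of Data analysis uses those totals in the comparison of the groups.

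**The concern.** The two steps of the predictor analysis do not appear to share an outcome. The stated aim, the definitions and the screening tests describe patients who are or are not adherent. The multivariable step then names a model for a continuous response.

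Linear regression on a 0/1 outcome estimates risk differences along an assumed straight line, and it can return fitted probabilities below 0 or above 1. If the regression is instead on a score, factors are selected against one outcome and modelled against another. In both cases the list of independent predictors, which is the product of this analysis, depends on a choice that the text leaves contradictory.

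A second, smaller matter is that allowance for pharmacy appears only in the multivariable models. The tests that decide which factors get there treat patients of the same pharmacy as independent.

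**Working it through.** The protocol gives no figure for this analysis, so there is none to reproduce. The check sets the statements side by side and then sizes the consequence.

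**1. Which outcome do the statements imply?**

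- Target: suboptimal adherence, defined only by cut-offs (Primary outcome measures). Sample size also treats nonpersistence as a state, namely having discontinued, and plans on percentages of patients (50% versus 65%).
- Mann-Whitney and t-tests are neutral. They can compare a factor between adherent and suboptimally adherent patients, or a score between the levels of a two-level factor.
- Chi-square is not neutral. It needs a categorical outcome, so it fits the cut-off and not a score.

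| Outcome meant | Chi-square screen | Linear regression |
|---|---|---|
| Cut-off (yes/no) | matches | does not match |
| Total score | does not match | admissible for TABS or MedsIndex |

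Neither row is consistent throughout.

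**2. Size, if the outcome is yes/no.** The inputs are assumptions except n = 450, the planned recruitment (Sample size). Model: logit P(Y=1) = b0 + b·x1 + 0.7b·x2, with two further covariates that have no effect. All four covariates are independent standard normal, there is no pharmacy effect, ordinary linear regression is fitted to Y, and there are 400 runs per row.

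| b0 | b | Prevalence | Fitted values outside 0-1 | Null covariate significant at 5% |
|---|---|---|---|---|
| 0 | 0.5 | 50.0% | 0.1% | 4.0% |
| 0 | 1.0 | 50.2% | 3.8% | 5.5% |
| 1.4 | 1.0 | 75.0% | 9.0% | 7.0% |
| 2.2 | 1.0 | 85.2% | 13.1% | 4.5% |

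The Monte Carlo standard error of a 5% rate is √(0.05 × 0.95 / 400) = 0.011, so 4% to 7% is compatible with the nominal level. A second simulation, with 448 patients and four log-odds slopes of 0.7, 0.5, 0.5 and 0.4, gave 2.3% of fitted values out of range with nonadherence near 50% and 9.7% with it near 20%.

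The effect scale shifts as well. If the truth is logistic with slope β, the local risk difference is β·p(1−p). For β = 1 this is 0.5 × 0.5 = 0.25 at p = 0.5, and 0.85 × 0.15 = 0.1275 at p = 0.85, a ratio of 0.25/0.1275 = 1.96. One straight-line coefficient averages over such differences.

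**3. Clustering in the screen.** There are 56 pharmacies (Abstract, Methods/Design), each asked for 7-10 patients (end of Exclusion criteria), and 450/56 = 8.04 patients per pharmacy on average. A test that ignores pharmacy understates the variance by a factor of roughly 1 + (8.04 − 1)·ρx·ρy = 1 + 7.04·ρx·ρy, where ρx and ρy are the intracluster correlations of the factor and the outcome. The protocol gives neither, so the size stays open. It is small for factors that vary mainly within pharmacies, and larger for factors that patients of one pharmacy share.

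**4. Form of the pharmacy term.** With 56 pharmacy indicators, one patient-level covariate and one pharmacy-level covariate, the design has 58 columns and rank 57. The pharmacy-level coefficient is then not estimable. This holds for a fixed 56-level factor and not for a random intercept or GEE.

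**The case against.** The strongest reply is that the yes/no outcome is inferred. The first paragraph of Data analysis works with total scores, and linear regression on the TABS or MedsIndex score is a legitimate analysis. That stands: the text does not prove a binary dependent variable. It does not remove the mismatch, because the chi-square screen and the cut-off definitions then belong to a different outcome from the one modelled.

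The reply also limits the harm, and this stands too. The aim is to identify factors, not to predict probabilities. The only rate used for planning is about 50%, where fitted values outside 0-1 are few. Prevalence well above 50% is still plausible, since the recruitment software preferentially picks patients with poor refill adherence and any MedsIndex score below 100 counts as suboptimal.

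Three stronger readings are tempting and are not supported:

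- A reader might infer that pharmacy-level predictors cannot be estimated. The text says only that "a pharmacy variable will also be included in the multivariate models". It does not say that the variable is a fixed factor, and it announces no pharmacy-level predictor.
- A reader might infer that the standard errors and p-values are invalid. The simulated false-positive rates are near nominal, though only for a null covariate unrelated to the others and without clustering.
- A reader might count selection by univariate p-value as an error in itself. It is a conventional exploratory approach, and objecting to it is largely a preference.

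**Conclusion.** The concern holds in a limited form. The stated method does not match the stated target, and on the alternative reading the screen does not match the model. This is a conflict within the text, not a detail left to an unseen analysis plan.

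If the outcome is yes/no, the cost is a poorly chosen effect scale and up to about 13% of fitted values out of range at 85% prevalence, with little effect on false positives in the setting examined. These figures rest on assumed prevalences and slopes. Neglect of clustering in the screen is real, but its size is unknown. A fixed 56-level pharmacy factor would block pharmacy-level effects, but that remains conditional on a form the text does not state.

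The analysis uses baseline data and is not among the listed primary or secondary outcomes. It does not affect the comparison of randomised groups or the sample size, so the point is a worthwhile correction of low consequence.

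**What to change.** 1. Name the dependent variable for each instrument: the cut-off or the score.
2. For suboptimal adherence or nonpersistence as a yes/no state, replace linear regression with logistic regression with a random pharmacy intercept, or with GEE clustered on pharmacy. Choose one in advance, because the first gives pharmacy-specific and the second population-averaged odds ratios.
3. Where a continuous score (TABS, MedsIndex) is the stated outcome, use a linear mixed model with a random pharmacy intercept.
4. If a screening step is kept, run it on the same outcome with the same allowance for pharmacy, for example as single-factor versions of the final model.
5. State the form of the pharmacy term. A random effect or GEE also keeps pharmacy-level factors estimable, should any be added.

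The cost is a few lines of text and standard software. No further data or patients are needed.

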**Methods/Design:**

The HAPPY trial is a multi-centre prospective randomised controlled trial. Fifty-six pharmacies have been recruited from three Australian states. To identify potential patients, a software application (MedeMine CVD) extracted data from a community pharmacy dispensing software system (FRED Dispense^®^). The pharmacies have been randomised to either 'Pharmacist Care Group' (PCG) or 'Usual Care Group' (UCG). To check for 'Hawthorne effect' in the UCG, a third group of patients 'Hidden Control Group' (HCG) will be identified in the UCG pharmacies, which will be made known to the pharmacists at the end of six months. Each study group requires 182 patients. Data will be collected at baseline, three and six months in the PCG and at baseline and six months in the UCG. Changes in patient adherence and persistence at the end of six months will be measured using the self-reported Morisky score, the Tool for Adherence Behaviour Screening and medication refill data.

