### Cluster randomisation

In each state, pharmacies were randomised to either Pharmacist Care Group (PCG) or Usual Care Group (UCG) according to the PhARIA. Randomisation was carried out at the pharmacy level to avoid the contamination likely to result from the same pharmacy recruiting and following up both intervention and control group patients. Randomisation was carried out at a central location using the sealed opaque envelope technique. To check for any 'Hawthorne effect' [20,21] in the UCG due to the effect of data collection, a third group of patients (Hidden Control Group - HCG) who are taking or have taken antihypertensives in the previous six months (but not included as participants in the UCG) will also be identified.

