### Exclusion criteria

• participation in other adherence promotion programs;

• having had a pharmacist-conducted HMR service in the last 12 months;

• unable to communicate in English; and

• does not self-administer antihypertensive medicines.

Each pharmacist was asked to recruit 7-10 patients from their pharmacy.

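### The tests named for the primary PCG–UCG comparison ignore the randomised pharmacies, and the only stated cluster adjustment belongs to a baseline model that estimates no arm effect

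*Protocol article*

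**What the plan says.** All references are to the protocol article.

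- **Cluster randomisation:** the pharmacy is the randomised unit. "Randomisation was carried out at the pharmacy level to avoid the contamination likely to result from the same pharmacy recruiting and following up" patients of both groups is the reason given, and allocation was made within state and remoteness category: "In each state, pharmacies were randomised to either Pharmacist Care Group (PCG) or Usual Care Group (UCG) according to the PhARIA".
- **Primary outcome measures:** "The primary outcomes of the HAPPY trial are changes in patient adherence and persistence at the end of six months", measured by the Morisky scale, TABS and refill data such as MedsIndex.
- **Data analysis, first paragraph:** for the PCG–UCG comparison of these scores, "Paired t-tests and/or Wilcoxon Signed Rank test will be used to compare changes in total scores". No pharmacy term is mentioned.
- **Data analysis, second paragraph:** this describes a different analysis. Baseline data from all participants are screened one variable at a time and then entered in a linear regression for predictors of nonadherence or nonpersistence. That paragraph ends with "To adjust for cluster randomisation, a pharmacy variable will also be included in the multivariate models".
- **Sample size:** 182 patients per group for 50% versus 65%, with no ICC or design effect.

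**The concern.** In each pharmacy the same staff enrol the patients, deliver the care and collect the baseline and six-month data. Outcomes of patients in one pharmacy may therefore be correlated, and arm does not vary within a pharmacy. A test that counts each patient as independent then takes its standard error from the wrong level of variation.

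The sentence on clustering does not repair this where it stands. The only multivariate analysis the article describes is the baseline predictor regression, which makes no randomised comparison. At stake is the validity of the p-value and confidence interval for the main result. With positive within-pharmacy correlation, the trial would declare a difference between arms too often when there is none.

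**Working it through.** **Inputs from the article.** There are 56 pharmacies ("Fifty-six pharmacies have been recruited from three Australian states"). The recruitment target is 7–10 patients each ("Each pharmacist was asked to recruit 7-10 patients from their pharmacy"). The sample size is 182 per group after dropout and 225 per group at baseline, for 50% versus 65%, two-sided 5% and 80% power.

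**Assumptions.** The article gives neither the split of pharmacies between arms nor an ICC. I assume an even split (28 per arm), equal cluster sizes and an ICC of 0.01 to 0.10. The ICC that matters is that of the outcome analysed, here the change score.

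**Step 1: the plan's own figure.** With pooled proportion 0.575, n = [1.96·√(2·0.575·0.425) + 0.842·√(0.5·0.5 + 0.65·0.35)]² / 0.15² gives 170 per group. The unpooled version gives 167. With the continuity correction the result is 183, within one patient of the stated 182. All three formulas assume independent patients, so the sample size holds no hidden allowance for clustering.

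**Step 2: cluster size.** Evaluable patients per pharmacy are 2·182/56 = 364/56 = 6.5. At recruitment the figure is 450/56 = 8.0.

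**Step 3: type I error.** The design effect is DE = 1 + (m − 1)·ICC with m = 6.5. The true type I error of a nominal 5% patient-level test is 2·[1 − Φ(1.96/√DE)]. A correct confidence interval is √DE times as wide.

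| Assumed ICC | DE | True type I error | Correct interval wider by |
|---|---|---|---|
| 0.01 | 1.055 | 5.6% | 3% |
| 0.02 | 1.110 | 6.3% | 5% |
| 0.05 | 1.275 | 8.3% | 13% |
| 0.10 | 1.550 | 11.5% | 24% |

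At 10 patients per pharmacy, the top of the target, the error is 6.1%, 10.4% and 15.5% at ICC 0.01, 0.05 and 0.10.

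**Step 4: simulation.** With 56 pharmacies of 7 patients and 8,000 runs per ICC, an independent-samples t-test rejected in 6.0%, 8.6% and 12.5% of runs at ICC 0.01, 0.05 and 0.10. The formula at m = 7 gives 5.7%, 8.6% and 12.1%. A t-test on pharmacy means stayed at 4.9% to 5.3%.

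**Step 5: power of a valid analysis.** The effective size per arm is 182/DE. At m = 7, ICC 0.05 gives 182/1.3 = 140 and about 72% power. ICC 0.10 gives 182/1.6 = 113.8 and about 63%. The same formula without continuity correction gives 83% at DE = 1. At ICC 0.01 (DE 1.06) power is still about 81%.

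**Step 6: which pharmacy term can serve in an arm model.** Intercept, arm and 55 pharmacy indicators make 57 columns, and their matrix has rank 56. Arm is constant within pharmacy, so its effect cannot be estimated beside fixed pharmacy indicators. This limits how the fix may be worded. It does not show that the plan intends such a model.

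**The case against.** **Intent to adjust is on record.** The aim named in "To adjust for cluster randomisation, a pharmacy variable will also be included in the multivariate models" is relevant mainly to an arm comparison, and the sentence speaks of models in the plural. A full analysis plan, not shown, may hold the detail. This stands in part: one should not infer that the authors overlooked clustering. But the article itself names unclustered tests for the primary comparison and describes no multivariate model for it.

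**Aliasing.** A reader might infer that the plan's own adjustment is aliased with arm. The article does not support that. It does not say how pharmacy is coded, it places the term in a model without a reported arm effect, and a pharmacy random intercept would not be aliased.

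**The baseline model.** A reader might also infer that the pharmacy term there is wrong. It is not: fixed pharmacy effects are a legitimate way to handle clustering for patient-level predictors.

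**Size.** The inflation depends wholly on an ICC that is not given. Taking changes removes stable differences between pharmacies, so the ICC of change may differ from that of the score itself. At 0.01 to 0.02 the excess is modest. This stands, which is why the result is a range.

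**The test.** The figures are for a two-sample test, whereas the article names paired tests. That also stands: the two-sample test is a stand-in for a comparison between arms, and the use of paired tests for that purpose is a separate matter.

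**Conclusion.** The point holds. The named tests for the PCG–UCG comparison do not respect the unit of randomisation, and the stated adjustment is not attached to them. Nothing elsewhere in the article compensates. Followed as written, the plan gives too small a standard error for the main result at any positive ICC.

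The size is conditional: true type I error of about 5.6% to 11.5% for assumed ICCs of 0.01 to 0.10. This rests on 28 equal-sized pharmacies per arm, 6.5 evaluable patients in each and a two-sample patient-level test. With an ICC of zero there would be no inflation.

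**What to change.** State that every PCG–UCG comparison uses a method that accounts for pharmacy:

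- **Scores:** a linear mixed model for the six-month score with arm, baseline score, state/PhARIA strata and a random intercept for pharmacy, with small-sample degrees of freedom based on the 56 pharmacies (for example Kenward–Roger). An analysis of pharmacy-level summaries is a valid alternative.
- **Adherent yes/no:** one clustered method chosen in advance, with its own small-sample correction. Kenward–Roger does not carry over to logistic models or GEE.
- **Coding:** say that pharmacy must not enter the arm model as fixed indicators.
- **Baseline predictor model:** its pharmacy term may stay.

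The change needs no new data or patients, but it is not free. Confidence intervals widen, and power at 182 per group falls below the stated 80% at moderate ICC (about 72% at 0.05 and 63% at 0.10 with 7 patients per pharmacy). The plan should acknowledge this.

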### Ethics

This project has been approved by the Human Research Ethics Committees of Monash University, Curtin University and The University of Melbourne, and the Human Research Ethics Network of Tasmania. All pharmacists and patient participants (in the UCG and PCG) provided written informed consent at the time of enrolment.

Approval to access dispensing data for the HCG was given on the basis that pharmacists have routine access to this data about their patients via the dispensing program and would use it in normal practice to routinely check their patient's history for actual or potential medication-related problems. The researchers will have access only to deidentified patient data.

### Study timeline

Trial start: June 2009

Baseline data collection: June-August 2009

Three-month data collection: October-November 2009

Six-month data collection: December 2009-January 2010

Data analysis: February 2010

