### Pharmacy Eligibility Criteria

Pharmacies that met all the following criteria were eligible to participate in the HAPPY trial:

• use the pharmacy dispensing program 'FRED Dispense^®^';

• agree to install a software application (MedeMine CVD) to identify patients who are using or have used antihypertensive medicines in the previous six months;

• have at least 40 patients who are currently using or have used antihypertensive medicines in the previous six months;

• have a private counselling area within the pharmacy where one-on-one consultation with a patient will be shielded from the public eye and ear;

• willingness and ability to attend project training either face-to-face or online;

• have time within the working week to allocate about one uninterrupted hour per patient to collect the baseline data; and

• able to follow-up participants for at least six months from baseline.

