### Inclusion criteria

• using or having used in the last six months at least one antihypertensive medication belonging to the four most common classes of antihypertensives in Australia - angiotensin converting enzyme inhibitors angiotensin-II receptor antagonists, calcium channel blockers, beta blockers -  http://www.aihw.gov.au/publications/cvd/mfchatua/mfchatua.pdf or fixed combinations of antihypertensive medications belonging to the above classes with other antihypertensives (e.g. diuretics);

• a diagnosis of primary hypertension;

• 18 years and above; and

• available for follow-up for at least six months from baseline.

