### Six-month visit (Final project visit)

Measures performed at baseline will be repeated for both UCG and PCG patients at their six-month visit to the pharmacy.

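### The printed timeline closes six-month data collection on 31 January 2010, before any patient enrolled in August 2009 has reached six months

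*Protocol article*

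**What the plan says.** The protocol article, under Study timeline, lists the collection periods in whole calendar months: "Baseline data collection: June-August 2009", "Three-month data collection: October-November 2009", "Six-month data collection: December 2009-January 2010" and "Data analysis: February 2010".

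Primary outcome measures fixes the time point: "The primary outcomes of the HAPPY trial are changes in patient adherence and persistence at the end of six months". The section on the six-month visit applies it to both arms: "Measures performed at baseline will be repeated for both UCG and PCG patients at their six-month visit to the pharmacy".

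Two eligibility criteria ask for the same length of follow-up. Patients must be "available for follow-up for at least six months from baseline" and pharmacies must be "able to follow-up participants for at least six months from baseline". The three-month visit is described for the Pharmacist Care Group (PCG) only.

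**The concern.** Intake is open for three months, but the six-month collection period lasts two and opens exactly six months after intake opens. The last month of intake therefore has no place in it. Taken literally, the schedule leaves two options for August patients: see them before six months, or leave them out of the primary analysis.

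Persistence depends on elapsed time, so an early final visit leaves less time to stop treatment. Leaving patients out costs sample size in a trial that needs 182 per group. The mismatch bears on the schedule of the primary outcome, so it deserves correction even though each August patient's shortfall is less than a month.

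**Working it through.** **Inputs.** Baseline 1 June to 31 August 2009, which is 30 + 31 + 31 = 92 days. Six-month collection 1 December 2009 to 31 January 2010. Analysis February 2010. Three-month collection 1 October to 30 November 2009. All are from Study timeline, with its months taken as whole months. Planned recruitment is 225 per group, 450 in total, and 182 per group are required (Sample size).

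**Step 1: due dates.** Due date = baseline date + 6 calendar months.

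| Baseline | Six months reached | Inside December-January? |
|---|---|---|
| 1-30 June | 1-30 December 2009 | yes |
| 1-31 July | 1-31 January 2010 | yes |
| 1-31 August | 1-28 February 2010 | no |

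So 30 + 31 = 61 enrolment days fit and 31 do not: 31/92 = 34%.

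**Step 2: shortfall if August patients are seen on the last day of the window.** A 1 August baseline is 1 day early (183 days of follow-up). A 28 August baseline is 28 days early. Baselines on 29, 30 and 31 August also fall due on 28 February, so they too are 28 days early. From 31 August to 31 January is 30 + 31 + 30 + 31 + 31 = 153 days, against 153 + 28 = 181 days to 28 February.

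The mean over August is (1 + 2 + ... + 28 + 3 × 28)/31 = (406 + 84)/31 = 490/31 = 15.8 days. Averaged over all 92 enrolment days it is 490/92 = 5.3 days.

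**Step 3: sensitivity to the meaning of six months.**

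| Six months read as | Enrolment days due after 31 January | Enrolment days due before 1 December |
|---|---|---|
| 6 calendar months | 31 of 92 (34%) | 0 |
| 182 days (26 weeks) | 29 of 92 (32%) | 1 |
| 168 days (24 weeks) | 15 of 92 (16%) | 15 of 92 (16%) |

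None of these readings makes the two windows fit.

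**Step 4: number of patients.** The article gives no accrual pattern. Affected patients = 450 × share enrolled in August. With even accrual (an assumption) this is 450 × 31/92 = 152. If August took one sixth of accrual it would be 75, and if it took half, 225. If August patients were omitted under even accrual, 225 × 61/92 = 149 per group would remain before any drop-out, below the 182 required.

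**Step 5: rough effect on persistence.** The Sample size section cites about 50% discontinuation within twelve months among patients starting treatment. If that rate is constant and carries over to this population (both assumptions), persistence is 0.5^(6/12) = 70.7% at six months and 0.5^(5/12) = 74.9% at five. That is about 4 points for a patient seen a full month early. For a whole arm with even accrual, the mean shortfall of 5.3 days gives about 0.707 × (ln 2/365) × 5.3 = 0.7 points, against a target difference of 15. If both arms accrue alike, the shift is similar in each.

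**Step 6: three-month window.** June baselines reach three months on 1-30 September, before the October-November window opens. July and August baselines reach it between 1 October and 30 November and fit. The three-month window thus matches a July-August intake and the six-month window a June-July intake. Only July fits both.

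**The case against.** The strongest reply is that Study timeline is a five-line project schedule in whole months, while patient-level timing is fixed elsewhere. The final measures belong to each patient's own six-month visit. On that reading some visits would simply run into February and analysis would start a little later. Visit tolerances are commonly left to the full protocol, so their absence here is no fault. This reply has weight: nothing in the article says that visits stop on 31 January or that patients would be measured early or dropped. But it resolves the conflict only by departing from the printed dates, which is what the correction asks for.

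The two eligibility criteria on follow-up concern availability and do not schedule a measurement, so they add little. The real conflict is between the timeline and the six-month endpoint and visit.

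A reader might infer more than the document supports:

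- **That the calendar cannot deliver six-month outcomes at all.** June and July baselines, 61 of 92 enrolment days, fit the window.
- **That follow-up length differs between arms and biases the comparison.** This would require the PCG and the Usual Care Group to enrol at different speeds, and nothing in the article shows that they did.
- **That refill scores become non-comparable.** MedsIndex is described as a score out of 100 per medicine based on refill history, with no look-back period stated. The effect of a visit about two weeks early cannot be worked out from that.
- **That the three-month misfit harms the primary outcome.** That visit is held in the PCG only, is not the primary time point, and enters no planned comparison in Data analysis.

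**Conclusion.** The timeline conflicts with the six-month endpoint for patients enrolled in August 2009, and only for them. They fall due on 1-28 February 2010, after collection is shown as closed and during the analysis month. Followed as printed, the schedule would measure them 1 to 28 days early or miss them.

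The dates need only calendar arithmetic. The share of patients does need an assumption: about a third holds under even accrual and six calendar months, and the share of enrolment days due too late falls to 16% if six months means 24 weeks. Measuring August patients slightly early would move the results little. Omitting them would be the more serious course. The point is worth correcting because it concerns when the primary outcome is collected and the correction is cheap. It is not evidence that the trial is biased.

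**What to change.** 1. Extend six-month collection to the end of February 2010, with some allowance for late attenders, or close baseline collection by 31 July 2009. The second option gives up 31 of the 92 enrolment days.
2. Start analysis after the last six-month visit rather than in a fixed calendar month.
3. State that each final visit, and the end date of the MedsIndex calculation, is counted from the patient's own baseline date.
4. As a secondary matter, reconcile the PCG-only three-month window with the June baselines, which fall due in September.

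With the extended window, the cost is about one month's delay to analysis and a corrected timeline. No new measurements are needed.
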